### Interim analyses {21b}

Not applicable since there will be no interim analyses regarding the main objective of the trial.

### Methods for additional analyses {20b}

In addition to the primary and secondary analyses outlined in the study protocol, we plan to conduct additional analyses to explore the treatment effect based on the frequency of application use as derived from log data. The treatment effect will be compared across different categories of application use, including weekly, biweekly, monthly, bimonthly, other, and no use. Specifically, “Weekly” will be defined as at least one use every week, while “other” will indicate less than one use in 2 months. “No use” will indicate zero or one use during the overall study period.

These additional analyses aim to provide insights into the relationship between the frequency of application use and treatment outcomes, allowing for a more nuanced understanding of the impact of mHealth intervention on blood pressure management in pregnant individuals with HDP.

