### Criteria for discontinuing or modifying allocated interventions {11b}

Participants have the autonomy to discontinue their involvement in the trial at any juncture without needing to provide further explanations. In the event of participant withdrawal, missing data will be handled through inverse probability weighting and worst-case imputation schemes as part of the sensitivity analyses. Additionally, no crossover from the control arm to the intervention arm will be permitted during the follow-up period. Furthermore, even in the event of crossover from the control arm to the intervention arm, follow-up will continue as per the intention-to-treat (ITT) analysis protocol.

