## Data collection and management

### Plans for assessment and collection of outcomes {18a}

For the assessment and collection of outcomes, baseline information will be collected by trained research nurses who will input the data into a web-based CRF at the time of study registration. Both groups will receive an OMRON blood pressure monitor, with the standard care group having their self-measured blood pressure automatically entered into the OMRON application via Bluetooth. In contrast, the group using Heart4U will have their measured blood pressure automatically synchronized with the application. The synchronized data will be seamlessly integrated with the web-based CRF, eliminating the need for additional data collection. Any errors or discrepancies in the data will be managed by an independent data committee, which is designed to notify stakeholders of any incorrect values.

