### Methods in analysis to handle protocol non-adherence and any statistical methods to handle missing data {20c}

In line with our study’s pragmatic approach and aim to assess real-world effectiveness, we have planned the analysis using the ITT principle. This approach allows us to evaluate the intervention effect while considering all participants according to their assigned group, regardless of protocol adherence.

In our study, which focuses on evaluating the effectiveness of a non-invasive intervention using a mobile health application rather than treatment, assessing non-adherence involves measuring compliance through log data generated by the mobile health application. We plan to conduct a sub-analysis specifically dedicated to examining compliance based on this log data. This approach allows us to quantify and evaluate non-adherence objectively.

For handling missing data, we will investigate the reasons behind their occurrence and determine whether they are independent of the outcome. Additionally, efforts will be made to retrieve lost information for patients who have not withdrawn consent. Multiple imputation methods will be prioritized over simple data imputation techniques due to their ability to generate imputations using regression models and create multiple imputed datasets, which helps reduce bias and improve variability estimation. Data imputation will be deemed reasonable under specific conditions, such as when the frequency of missingness is low, the outcome variable holds clinical significance, and viable strategies for imputation are available.

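### Comparing the treatment effect across app-use classes yields a non-randomised association, and the classes overlap and depend on length of follow-up

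*Protocol article*

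**What the plan says.** Methods for additional analyses {20b} announces "additional analyses to explore the treatment effect based on the frequency of application use as derived from log data" and continues: "The treatment effect will be compared across different categories of application use, including weekly, biweekly, monthly, bimonthly, other, and no use". The section links these analyses to the impact of the intervention on blood pressure management.

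Three of the six classes are defined. *Weekly* requires use in every week. For the residual class the text reads "other” will indicate less than one use in 2 months". The class *no use* "will indicate zero or one use during the overall study period".

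Two other sections fix what the control arm can contribute. Plans for assessment and collection of outcomes {18a} describes data capture "with the standard care group having their self-measured blood pressure automatically entered into the OMRON application via Bluetooth". Criteria for discontinuing or modifying allocated interventions {11b} says "no crossover from the control arm to the intervention arm will be permitted during the follow-up period".

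Statistical methods {20a} applies the intention-to-treat principle to every analysis, and {20c} repeats it for the evaluation of effectiveness.

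**The concern.** A treatment effect is a contrast between randomised groups. Here the groups are formed by what women in one arm did after allocation. No control participant can have a Heart4U log, so a use class can only be set against all controls or against other users. Randomisation protects neither comparison. A contrast by achieved use also cannot meet the article's own statement that intention-to-treat governs all analyses.

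Two further problems lie in the definitions. Some women belong to two classes at once. And because one class is a count over the whole study while another requires use in every week, a woman's class depends on how long she was followed as well as on how often she used the app.

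At stake is what the trial may conclude. A gradient across use classes, reported under the name treatment effect, would read as a dose-response of the app when it may only reflect which women keep using it and for how long they were observed.

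**Working it through.** **Inputs.** Sample size {14} gives a target difference of 3.2 mmHg, an SD of SBP change of 13 mmHg, a control-arm fall of 16 mmHg, 80% power and 261 per arm; alpha is 0.05, two-sided by {20a}. The correlation r between engagement and SBP fall, the share of women in each class, the weekly probability of use and the follow-up lengths are not in the document. They are assumptions, shown as ranges or examples.

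**1. The plan's own figure.** n per arm = 2 × (1.960 + 0.842)² × 13² / 3.2² ≈ 259, or 260 rounded up. The t-based solution is 260.04, which rounds up to 261. Then 522 / 0.90 = 580. The sample size reproduces, so 3.2 and 13 mmHg serve as yardsticks.

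**2. Overlap.** Taking 2 months as 8.7 weeks, the rate per 2 months is uses / (weeks / 8.7).

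| Follow-up | Zero uses | One use: rate per 2 months | One use falls in |
|---|---|---|---|
| 6 weeks | *no use* and *other* | 1.45 | *no use* by count; bimonthly or more by rate |
| 8 weeks | *no use* and *other* | 1.09 | *no use* by count; bimonthly or more by rate |
| 12 weeks | *no use* and *other* | 0.72 | *no use* and *other* |
| 20 weeks | *no use* and *other* | 0.43 | *no use* and *other* |
| 30 weeks | *no use* and *other* | 0.29 | *no use* and *other* |

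**3. Dependence on follow-up.** Follow-up runs from enrollment to about 1 month after birth, so it varies with gestation at enrollment. Eligibility {10} admits at-risk women and chronic hypertension as well as preeclampsia after 20 weeks.
- The *weekly* rule is harder to meet over a longer period. With a 95% chance of use in any week, 0.95^8 = 66% meet it over 8 weeks and 0.95^28 = 24% over 28 weeks.
- The *no use* rule works the other way, because a count of zero or one is more easily reached in a short follow-up.

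For the first route, suppose 25% are early-enrolled at-risk women (28 weeks, fall 8 mmHg), 75% are late-enrolled hypertensive women (8 weeks, fall 16 mmHg), and the app does nothing.
- Weekly users: (0.75 × 0.663 × 16 + 0.25 × 0.238 × 8) / (0.75 × 0.663 + 0.25 × 0.238) = 15.1 mmHg.
- All others: (0.75 × 0.337 × 16 + 0.25 × 0.762 × 8) / (0.75 × 0.337 + 0.25 × 0.762) = 12.6 mmHg.

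The unrounded gap is 2.6 mmHg. Varying the at-risk share from 25% to 50% and their fall from 0 to 8 mmHg gives 2.6 to 6.9 mmHg.

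**4. Gradient with a null app.** Let SBP fall = 16 + 13 × (rL + √(1 − r²) e), where L is latent engagement cut into six ordered classes. The gap between top and bottom class is r × 13 × (E[L | top] − E[L | bottom]). For six equal classes this is r × 13 × (1.50 + 1.50) ≈ 39r.

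| Class shares (assumed) | r = 0 | r = 0.05 | r = 0.10 | r = 0.20 | r at which gap = 3.2 |
|---|---|---|---|---|---|
| Six equal | 0 | 1.9 | 3.9 | 7.8 | 0.08 |
| 60% weekly | 0 | 1.8 | 3.5 | 7.0 | 0.09 |
| 40% no use | 0 | 2.0 | 3.9 | 7.9 | 0.08 |
| 30% at each end | 0 | 1.5 | 3.0 | 6.0 | 0.11 |

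Gaps are in mmHg. In 1,500 simulated null-app trials per setting, with 261 women in the Heart4U arm, a linear trend test at 0.05 was significant in about 5% at r = 0, 26–34% at r = 0.10 and 77–87% at r = 0.20.

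**5. Precision.** Six equal classes hold 261 / 6 = 43.5 women each. Against 261 controls, SE = 13 × √(1/43.5 + 1/261) = 2.1 mmHg, giving 32% power for 3.2 mmHg.

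**The case against.** The strongest defence is that the article calls these analyses additional and exploratory and elsewhere describes their aim as the relation between frequency of use and outcomes, which is an association. No decision rule rests on them. This stands: the problem is one of labelling and definition, and the primary comparison is untouched. A reader might infer that the trial's efficacy conclusion is compromised; nothing in the document supports that.

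A second defence is that *other* is plainly a residual class and *no use* takes precedence, a detail that an analysis plan could settle. Precedence would remove the double membership. It would not remove the dependence on follow-up, nor the placing of a woman who used the app once in 6 weeks among non-users. Such women should also be uncommon, since {11a} has staff contact anyone with fewer than three log-ins in 2 weeks. That is fair, though it also means that use is partly driven by the trial itself.

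A third defence is that r has no source in the document. This is right, and the size is therefore conditional. Against all controls rather than other users the artefact is smaller: for the top third of users it is 13 × 1.091 × r, or 2.8 mmHg at r = 0.2, below the 3.2 mmHg target, and 4.3 mmHg at r = 0.3. A reader might infer that an ineffective app is bound to show a gradient larger than the target effect; that does not follow.

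It is also tempting to say that sicker women enrolled late will fill the low-use classes and flatter the app. No section says so, and the *weekly* rule pushes the other way.

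Finally, {20c} says "We plan to conduct a sub-analysis specifically dedicated to examining compliance based on this log data". That sub-analysis measures adherence and claims no effect, so it is not part of the fault.

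**Conclusion.** The point holds in a limited form. The article fixes a comparison of the treatment effect across classes that are formed after randomisation and cannot exist in the control arm, so whatever gradient appears is a non-randomised association. The overlap between *other* and *no use*, and the dependence of class on follow-up length, follow directly from the stated definitions and need no assumption beyond variable follow-up.

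The numerical size does rest on assumption. In the six-class model a null app yields a top-to-bottom gap of 3.2 mmHg once engagement and SBP fall correlate at about 0.08 to 0.11, roughly 1% of outcome variance, and yields none at r = 0. The net direction of bias is uncertain. The analysis should be corrected because it governs how use data may be interpreted, but it does not bear on the validity of the primary test.

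**What to change.** In Methods for additional analyses {20b}, replace the comparison of treatment effects with text along these lines:

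> Within the Heart4U arm, SBP change will be described by rate of application use, adjusted for enrollment SBP, HDP category and gestational age at enrollment. These are descriptive associations and will not be reported as treatment effects. Rate is the number of uses divided by length of follow-up, in mutually exclusive classes: zero use; above zero but less than once per 2 months; once per 2 months to less than once per month; once per month to less than once per 2 weeks; once per 2 weeks to less than once per week; once per week or more.

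The cut points keep the article's own class names, reading biweekly as once in 2 weeks. Report follow-up length by class as well. With less than 2 months of follow-up a single use already gives a rate of at least one per 2 months, so rates reduce the dependence on follow-up without abolishing it.

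A complier average causal effect, with randomisation as the instrument, may be added as an optional sensitivity analysis but need not replace the description. Its exclusion restriction must be stated. Under {11a}, women below any use threshold still receive the app, education, contact from staff and clinician review of app data, so assuming no effect of assignment in them is doubtful.

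The cost is a change of wording and a few lines of code on log data that the protocol already plans to use. It is best made before outcome data are examined. The downside is that the use analysis can no longer be presented as evidence that the app works.

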### Methods in analysis to handle protocol non-adherence and any statistical methods to handle missing data {20c}

In line with our study’s pragmatic approach and aim to assess real-world effectiveness, we have planned the analysis using the ITT principle. This approach allows us to evaluate the intervention effect while considering all participants according to their assigned group, regardless of protocol adherence.

In our study, which focuses on evaluating the effectiveness of a non-invasive intervention using a mobile health application rather than treatment, assessing non-adherence involves measuring compliance through log data generated by the mobile health application. We plan to conduct a sub-analysis specifically dedicated to examining compliance based on this log data. This approach allows us to quantify and evaluate non-adherence objectively.

For handling missing data, we will investigate the reasons behind their occurrence and determine whether they are independent of the outcome. Additionally, efforts will be made to retrieve lost information for patients who have not withdrawn consent. Multiple imputation methods will be prioritized over simple data imputation techniques due to their ability to generate imputations using regression models and create multiple imputed datasets, which helps reduce bias and improve variability estimation. Data imputation will be deemed reasonable under specific conditions, such as when the frequency of missingness is low, the outcome variable holds clinical significance, and viable strategies for imputation are available.

### Plans to give access to the full protocol, participant-level data, and statistical code {31c}

The full study report, the anonymized data set, and the statistical code will be made available from the corresponding author upon reasonable request after the main results have been published and as long as it corresponds with the local regulations for data.

## Oversight and monitoring

### Composition of the coordinating center and trial steering committee {5d}

This study is conducted at a single site, eliminating the need for coordination between multiple centers. As a result, there is no independent oversight committee involved in monitoring the trial. However, the Principal Investigator (PI), [name], will hold regular meetings with the management team, co-investigators, and the data and safety monitoring board to ensure effective management and oversight of the trial.

### Composition of the data monitoring committee, its role, and reporting structure {21a}

The Data Monitoring Committee (DMC) for this study consists of three members experienced in cardiology, obstetrics and gynecology, and data analysis. These experts are from the same institution and have direct access to electronic medical records, enabling efficient communication for resolving discrepancies and troubleshooting issues. They are blinded and unbiased, ensuring impartial review of suspected clinical endpoints and adverse events.

The role of the DMC is to conduct a thorough review of suspected clinical endpoints and adverse events. Their objective is to standardize the review process for clinically relevant endpoints and minimize bias and variability from investigators involved in the study. As independent members, they operate free from any influence or regulations by the PI.

The reporting structure involves regular meetings between the DMC members to discuss and evaluate the data collected from the study. They provide recommendations and insights to the PI and the study management team based on their findings, contributing to the overall monitoring and oversight of the trial.

### Adverse event reporting and harms {22}

Given the nature of the intervention in this trial, no adverse events are anticipated to result directly from the intervention. The study involves self-monitoring through a mobile application, which does not entail invasive or harmful procedures. Additionally, as an open-label study, continuous monitoring by the attending physician throughout the trial ensures prompt identification and management of any potential concerns, minimizing associated risks.

However, it is crucial to acknowledge the potential risks inherent in using mobile health applications, particularly concerning privacy and security. To address these concerns, several measures are implemented. Firstly, data collection is conducted primarily using de-identified data to safeguard participant privacy. Furthermore, researchers collect only the minimum necessary data required for the research, reducing the risk of re-identification. Robust security protocols, including encryption and access controls, are employed to protect against unauthorized access or disclosure of sensitive information.

To mitigate the risk of misinterpretation due to inaccurate or incomplete information, the DMC is responsible for the meticulous review of all data collected, providing recommendations to the management team to ensure the integrity and accuracy of the study findings. This proactive approach enhances transparency and rigor in data interpretation, further safeguarding participant well-being and study integrity.

### Frequency and plans for auditing trial conduct {23}

The DMC has agreed to meet at the conclusion of each data collection period to review the trial conduct. Additionally, they will inform the research team of any issue as they arise. Furthermore, the research team will convene every 2 weeks for a trial review.

### Plans for communicating important protocol amendments to relevant parties (e.g., trial participants, ethical committees) {25}

Important protocol modifications were communicated to the research ethics committee and, if necessary, to the trial participants.

### Dissemination plans {31a}

The trial results will be disseminated nationally and internationally to reach participants, academic researchers, and the public upon completion of the trial. Dissemination activities will include scientific presentations at conferences and publication in peer-reviewed journals. However, to uphold the scientific integrity of the trial, data will not be released for publication or oral presentation purposes before the end of the trial without the permission of the PI.

## Discussion

HDP is recognized to be closely related to adverse pregnancy outcomes [19, 20], and its impact extends beyond maternal health and has implications for postpartum cardiovascular outcomes [21]. Therefore, the proactive management of HDP is of paramount importance. However, the current landscape is limited by fetal safety issues, which constrain pharmaceutical interventions within this context [7, 8]. Although addressing HDP is essential for both maternal and fetal well-being, a cautious approach to medication underscores the complexity of balancing therapeutic benefits with potential risks to the developing fetus [22].

Recognizing advancements in technology, hypertension management extends beyond conventional pharmaceutical interventions. Self-management of hypertension through platforms such as mHealth have emerged, enabling patients to actively monitor and regulate their blood pressure while facilitating communication with healthcare providers [23–25]. In addition to traditional pharmacotherapy, the integration of innovative tools such as mHealth has demonstrated the potential to achieve proactive blood pressure control and, in certain studies, even yield improvements in cardiovascular outcomes [10].

This study was meticulously designed to capitalize on the advantages of mHealth to effectively support blood pressure control in individuals with HDP, a population in which the availability of pharmaceutical interventions may be limited. Through the utilization of the Heart4U application, we aspire to enhance participant awareness of their blood pressure status and facilitate seamless communication with healthcare providers. This approach serves as a dual-fold strategy. First, by empowering proactive blood pressure management, we seek to amplify individual engagement in health outcomes. Second, we anticipate that this endeavor will translate into improved maternal and fetal outcomes, ultimately extending to a potential influence on postpartum outcomes as well.

By embracing a non-invasive intervention model that employs smartphones, a tool familiar to most individuals, this study strives to foster regular health monitoring. The Heart4U application, integrated with medical services, not only facilitates effective communication with health professionals, but also allows for convenient follow-up outside the clinical setting. As a result, we anticipate minimal adverse effects, while expecting to reap a multitude of benefits. This innovative approach uses modern technology to empower patients, augment awareness, enhance communication, and potentially trigger positive health outcomes.

In conclusion, this study highlights the significance of proactive management for HDP and introduces the innovative potential of mHealth solutions, such as the Heart4U application. This study aims to investigate a pathway for improving maternal, fetal, and postpartum outcomes in patients with HDP by enhancing blood pressure control and facilitating effective communication. Our study seeks to provide valuable insights into the effectiveness of these interventions, contributing to the advancement of maternal healthcare practices.

## Trial status

Publication based on Protocol V1.0, 16 Aug 2023. The study center is open to recruitment starting from September 2023. Recruitment is anticipated to conclude by August 2026, with the study expected to be fully completed, including data collection, by June 2027.

